## Sampling Method and Sample Size Estimation

Eligible PD patients will be recruited using a purposive sampling method. A group of 10 pairs will be recruited for this study (10 caregivers and 10 patients per group) based on the latest recommendation by Whitehead et al. (2016) for a minimum of 10 participants per trial arm for pilot study.

## Study Procedure

1. Explanation about the study will be provided using information sheet as attached in appendix 9 and eligible PD patients and family-caregivers will be requested to sign an informed consent form prior to participation in the study.
2. Data on social-demography will be compiled and baseline measurements of functionality, mobility and QoL of persons with PD, caregiver knowledge, burden and QoL will be conducted and analyzed to ensure the two groups are comparable at baseline.
3. The participants will then be randomly allocated into either the experimental group or the control group using ‘sealed opaque envelope’ technique by health personnel blinded to the study.
4. Training sessions will be conducted by a group of multidisciplinary health care team at the Physiotherapy Unit of UKMMC and family caregivers will be required to demonstrate the components. Training module booklet containing a multi-component training materials will be provided to facilitate care at home and the content of the module consisting of multi-care physical and psychosocial tasks and guidance on health care for PD patients will be established based on findings of FGD.
5. The experimental group will receive a structured, comprehensive family training programme while the control group will receive usual intervention which normally consist of advice from treating medical officers and usual therapy program by rehabilitation professionals as necessary. The usual program consists of physiotherapy (functional training, strength and balance training) and occupational therapy (activities of daily living training and self- care).
6. Both groups will receive the interventions on a weekly basis for 12 weeks and followed-up (telephone) weekly to ensure compliance and monitor any arising problems or adverse effects.
7. Measurement of outcomes will be done at week 0 and 12 of the intervention, while program feasibility and acceptance will be assessed at week 12 as depicted in Figure 5.

Will be excluded based on

exclusion criteria

Persons with PD and their family caregivers will be screened in medical rehabilitation department of UKMMC (n=40)

Eligible participants will be randomized based on simple random sampling (n=40) and baseline measurement will be taken

[figure not shown]

[figure not shown]

[figure not shown]

[figure not shown]

[figure not shown]

[figure not shown]

Assessment of outcomes after 12th week

Functions and mobility measured using TUG and MDS-UPDRS respectively

QoL of patient and family caregivers measured using EQ-5D.

Caregiving burden measured using Zarith Burden

Interview.

Knowledge of carer measured using adapted , translated and validated questionnaire Feasibility and acceptance assessment

Assessment after 12th week

(n=40), intention to treat approach)

Allocated to control group; usual intervention (n=20)

Allocated to experimental group; family caregiver training module (n=20)

Training will be given to caregivers before intervention

Results compilation and reporting

Figure 5 Flow Chart of Phase II

## Outcome measurement tools for pilot RCT

All outcome assessment will be conducted by a blinded assessor at week 0 (pre intervention) and week 12. Feasibility and acceptance assessment will be evaluated based on the clinical effects, rate of adherence, drop-outs and feedback from the program participants only after week 12. Clinical effect outcomes measured on persons with PD and family caregivers are summarized in Table 3. Description and psychometric properties of the outcome measures are depicted in detailed in summative evaluation. Sample of outcome measurement tool is attached in the Appendix 10.

Table 3 Outcome measures used for family caregivers and persons with PD

| **Persons with PD variables** | **Outcome measurements tools** |
| --- | --- |
| I. Mobility | Timed Up and Go (TUG) test |
| II. Motor and non-motor functions | The Movement Disorder Society-Sponsored Revision of the Unified Parkinson's Disease  Rating Scale (MDS-UPDRS) |
| III. QoL | EQ-5D |
| **Family Caregivers of Persons with PD**  **variable** | **Outcome measurements** |
| I. Knowledge level of carer | Adapted and translated from study by  Moore and Knowles, 2006 |
| II. Caregiving burden | Zarith Burden Interview |
| III. QoL | EQ-5D |

## Statistical tools for pilot RCT

Formative evaluation of pilot RCT will adhere to the same statistical tool depicted in section

7.4.8 of statistical tools in summative evaluation. Summary of the statistical tests used as per objective is highlighted in Table 4.

Table 4 Statistical tests mapped to objectives for phase II

| **Objectives** | **Statistical test** |
| --- | --- |
| To develop the structured multi-component family-training  program and determine its feasibility and acceptance |  |
| Clinical effects | 6x2 Mixed Model ANOVA |
| Number of drop outs Adherence Feedback  Adverse events | Descriptive statistics (Mean, standard deviation and percentage) |

## PHASE III – Implementation and summative evaluation

Phase III involves implementation of the module through an assessor blinded RCT and a summative evaluation.

## Study design

A single-blind RCT followed by a costing analysis.

## Target Population

The target population in this study is PD patients of stage I and II, and their family caregiver.

## Eligibility Criteria INCLUSION CRITERIA:

1. PD patients
   1. Age 50-75 years old
   2. Stage I and II of Parkinson’s disease based on HY scale
   3. Availability of family caregivers.
2. Family caregivers
   1. Main caregiver who lives with the PD patient

## EXCLUSION CRITERIA:

1. PD patients
   1. Impaired physical function due to other conditions such as a recent fracture within the past 6 months, severe arthritis or other neurological disease such as peripheral neuropathy.
   2. Have medical illness limiting participation in exercise, such as unstable angina and uncontrolled hypertension.
2. Family caregiver:
   1. Providing part-time caregiving due to availability of maid/helper
   2. Presence of clinically diagnosed depression with a cutoff point of ≥16 in CES-D.
   3. Presence of mild cognitive impairment or dementia with a cutoff point of ≤26 in MoCA.

## Sampling Frame

Main sampling frame for this study phase is all persons with PD registered with the MPDA or persons with PD referred to the Medical Rehabilitation Services Department of UKMMC since January 2021 and their main family caregiver. MPDA registry and patient’s registry maintained by the neurology rehabilitation unit of the department will be accessed to identify persons with PD.

## Sampling Method and Sample Size Estimation

Eligible persons with PD will be recruited using a non-probability purposive sampling method. Selected participants (persons with PD) will then be allocated into either the test group (family-training program) or the control group (usual intervention) using simple randomization method. Sample size is calculated using Gpower software version 3.1. This study will use 6x2 Mixed Model Anova with post hoc analysis using Bonferroni. Therefore F-test (ANOVA repeated measures, within-between interactions) is chosen in Gpower software. Study power is set at 95%, alpha set at 0.05 and effect size of 0.41 was chosen based on the effect sizes for the primary outcomes of clinical interest from the study by Bueno et al. (2017). Based on sample size calculation, a total of 18 participants are required. Hence a minimum of nine PD patients and nine family caregivers (n=18 per group) will be recruited in each group which makes it a total of 36 participants in this study. Dropouts are not considered because intention-to-treat analysis will be used and all participants who are enrolled at baseline will be included in the final analysis.

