## Statistical Tools

Statistical Analysis Statistical Package for Social Sciences (SPSS) will be used and variables will be analyzed descriptively, presenting mean and standard deviation. Intention to treat analysis will be performed. Effects of the interventions and comparison between groups will be analyzed using 6 x 2 Mixed Model ANOVA. The level of significance is set at *p*<0.05. Mixed model ANOVA will provide results for main effect of time (before and after therapies), main effect of group (experimental and control group), time and group interaction effect. Statistically significant main effect of time highlights significant changes in the dependent variables following interventions. Statistically significant main effect of group highlights the significant difference between experimental and control groups on the outcomes. Statistically significant time and group interaction effect highlights if experimental group yield the desired effect on dependent

variable significantly compared to control group (Field 2009). Besides aforementioned effects, partial eta squared (ηp²) will also analyzed to display the degree of influence of the independent variable. Cohen (1988) stated that the effect is large for ηp²≥0.14, medium for 0.14>ηp²≥0.06 and small for ηp²≤0.01. Comparison of costs of the two interventions will be done using independent samples *t* test. Statistical tests mapped to objectives in phase III is presented in Table 6.

Table 6 Statistical tests mapped to objectives for phase III

| **Objectives** | **Statistical test** |
| --- | --- |
| To compare the pre and post score of functions, mobility and QOL between persons with PD receiving the structured multi-component family-training program and control group.  To compare the pre and post score knowledge, QOL and burden between family members of persons with PD receiving the structured multi-component family-training  program and control group. | 6x2 Mixed Model ANOVA |
| To evaluate the cost effectiveness of the structured multi-  component family-training program and control group. | Independent sample *t* test |
| To determine the sustainability of the structured multi- component family-training program among the family of  persons with PD. |  |
| - Retention of effect | 6x2 Mixed Model ANOVA |
| - Compliance - Adherence - Drop outs | Descriptive statistics (Mean, standard deviation and percentage) |

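### Pilot and Phase III recruit families by purposive sampling with no stated order of approach and no planned count of families approached, so uptake cannot be computed and the descriptive acceptance, adherence and dropout rates are open to favourable selection

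*Protocol*

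**What the plan says.** **Recruitment.** In the pilot (Sampling Method and Sample Size Estimation), "Eligible PD patients will be recruited using a purposive sampling method". In Phase III (section of the same name), "Eligible persons with PD will be recruited using a non-probability purposive sampling method". Neither section gives a selection rule beyond eligibility or an order of approach.

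**Frame.** Under Phase III, Sampling Frame, the frame is set out as follows: "Main sampling frame for this study phase is all persons with PD registered with the MPDA or persons with PD referred to the Medical Rehabilitation". For the hospital source, only referrals from January 2021 onward count. On how patients are found, the section says that both registries will be used, the hospital one being "maintained by the neurology rehabilitation unit of the department will be accessed to identify persons with PD". The pilot's Sampling Frame is the same in substance.

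**Allocation.** After selection, Phase III participants "will then be allocated into either the test group (family-training program) or the control group (usual intervention) using simple randomization method". Figure 5, for the pilot, words this step as "Eligible participants will be randomized based on simple random sampling (n=40"); Figure 6 has the same wording with 36.

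**Flow counts.** Figure 5 shows 40 screened and 40 randomised. Figure 6 shows 36 and 36. Each also has a box for people removed under the exclusion criteria.

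**Use of the rates.** Specific objective 4 covers feasibility and acceptance, and objective 8 covers sustainability. Dropouts, adherence and feedback (Table 4) and compliance, adherence and dropouts (Table 6) are summarised by "Descriptive statistics (Mean, standard deviation and percentage"). The alternate hypothesis asserts that the programme is sustainable and well accepted.

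**The concern.** A treatment contrast within randomised families does not need those families to be representative. A statement that a programme is accepted, adhered to and sustained does, because it describes the families to whom the programme would be offered. If the choice of whom to approach is left open, those rates describe whoever happened to be approached. If refusals are not counted, nobody can later judge how far that group differs from the registries.

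At stake is the meaning of part of objectives 4 and 8. For a feasibility pilot, the share of eligible families who agree to join is itself a main result, and nothing in the plan produces it. The gap cannot be closed afterwards, because refusals that were never logged are lost.

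**Working it through.** **1. Does the sampling method enter the plan's own sample size?** Inputs from Phase III, Sampling Method and Sample Size Estimation: effect size f = 0.41, alpha 0.05, power 95%, repeated-measures ANOVA with within-between interaction, 2 groups. There are 3 measurement times (week 0, week 12, 6 months). The Protocol gives neither the correlation between measurements nor a sphericity correction; I assume 0.5 and 1.

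- Noncentrality = N × m × f² / (1 − ρ) = 18 × 3 × 0.1681 / 0.5 = 18.15
- Degrees of freedom = (2 − 1)(3 − 1) = 2 and (18 − 2)(3 − 1) = 32
- Power = 0.962, and 18 is the smallest even total that reaches 0.95

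The stated 18 is reproduced under these assumptions (9 patients per arm; 36 people with their caregivers). The sampling method is not an input, so changing it alters no stated figure.

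**2. How much room is there for choice?** The Phase I needs analysis uses a population size of 400 in its sample size formula, for stage I and II patients from the same two sources. The pilot needs 20 pairs, 20/400 = 5%. Phase III needs 18 pairs, 18/400 = 4.5%. These percentages are a lower guide only: the RCT phases limit UKMMC referrals to those since January 2021 and add caregiver exclusions, so the eligible pool is smaller than 400.

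**3. Can uptake be computed?** Uptake = randomised / (approached and eligible). No count of families approached or declining is planned. The nearest figures are the screened counts, which give 40/40 = 100% and 36/36 = 100% by construction. They can be right only if nobody screened is ineligible or declines, which sits badly with the exclusion box in each chart.

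**4. Which results are exposed?**

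| Result | Source | Exposed to selection? |
| --- | --- | --- |
| Clinical effects; retention of effect | Mixed-model ANOVA, Tables 4 and 6 | No, as a between-arm contrast |
| Dropout and compliance compared between arms | Both arms followed weekly | No, as a contrast |
| Dropout as a rate for the programme | Tables 4 and 6, descriptive | Yes |
| Acceptance of, and adherence to, the module | Tables 4 and 6, descriptive; experimental arm only | Yes |

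**5. Direction.** Among eligible families willing to take part, let t be the proportion who would adhere, and let r be how many times as likely such a family is to be approached as one that would not. The adherence seen is t·r / (t·r + 1 − t). Take t = 60% as an assumption:

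- r = 1: 60% adhere, 40% do not (no bias)
- r = 1.5: 0.90/1.30 = 69% adhere, 31% do not
- r = 2: 1.20/1.60 = 75% adhere, 25% do not
- r = 3: 1.80/2.20 = 82% adhere, 18% do not

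Favourable selection therefore raises adherence and lowers dropout. Neither t nor r can be taken from the documents, and r below 1 would reverse the direction. This shows direction, not size.

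**6. Background imprecision.** These rates are imprecise under any sampling method. With no dropouts among 10 pairs the exact 95% interval is 0 to 31%, and among 9 pairs 0 to 34%.

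**The case against.** The strongest reply is that purposive here means little more than recruiting people who meet the criteria. The FGD flowchart section and the expert recruitment under Module development both tie the word to eligibility criteria, and the RCT sections speak of eligible persons. On that reading this is ordinary consent-based trial recruitment. That is a fair reading, and it rules out saying that families are hand-picked: no text says they are chosen for motivation. It does not supply an order of approach, which remains open.

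Second, the counts in Figures 5 and 6 are planned targets, and some elements of both charts could not be read. Equal targets do not prove that refusals will go unrecorded, and a log may be kept in practice. What remains is that the legible text plans no such count and that the screened numbers leave no room for exclusions.

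Third, consenters alone are randomised under any method, so fixed-order invitation would not yield rates for all eligible families. This is correct. It would remove staff choice as a source of selection and make self-selection visible through the refusal count.

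A reader might also infer more than the documents support:

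- That the rates have no comparator. Dropout and compliance do: a randomised control arm followed weekly. Only acceptance of and adherence to the module lack one, which is inherent.
- That the rates have no denominator. Numbers randomised are given (20 people per arm in the pilot, 18 in Phase III). What is missing is the number approached.
- That the registries are complete. The Protocol says only that they will be accessed.
- That these rates decide the move from pilot to Phase III. No progression rule or threshold is stated.
- That Figure 5 promises random selection from the registries. Its wording describes allocation of people already found eligible, and should be aligned with the text.

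**Conclusion.** The point holds as a cheap improvement of minor severity. Both RCT phases fix a non-probability method with no order of approach although registries will be accessed, and neither plans the counts needed for uptake. No treatment contrast is biased by this, and neither the sample size nor the analysis is affected. The exposure is confined to the descriptive part of objectives 4 and 8: acceptance and adherence may be too high and dropout too low as descriptions of eligible registry families.

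The size cannot be estimated. It depends on how families are in fact approached, which the Protocol does not say, and is nil if approach is unrelated to likely adherence. The conclusion rests on reading purposive as leaving the choice open. If the investigators in practice invite every eligible family in turn, the remaining defects are the wording and the missing counts.

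**What to change.** In both Sampling Method and Sample Size Estimation sections (pilot and Phase III), replace purposive sampling with this rule: merge the two registry lists, remove duplicates, and invite eligible patient-caregiver pairs in a fixed consecutive or random-number order until the target number is randomised. Keep a log of pairs approached, ineligible (with reason), declining (with reason if given) and randomised. Replace the screened counts in Figures 5 and 6 with counts that allow for exclusions and refusals, and call the allocation step randomisation, not sampling. Report uptake, randomised over approached and eligible, as a feasibility result beside the Table 4 and Table 6 summaries.

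The cost is protocol wording and a log. Arms, outcomes, numbers and tests do not change. Recruitment may be slower and the reported rates less favourable.

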## HYPOTHESIS

- 1. **Null Hypothesis**

The structured multi-component family-training program is not more effective clinically and by cost, when compared with a usual intervention in improving functions, functional mobility and QoL of persons with PD, carer knowledge, carer QoL and burden among family members of PD when compared to the usual intervention. The family-training program is not sustainable and not well accepted by family and people with PD.

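### Phase III names no primary outcome and no success rule: six outcomes are each tested at p<0.05, and the alpha, power and N=18 are tied to none of them

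*Protocol*

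**What the plan says.** The relevant statements are all in the Protocol.

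- **Sample size (Phase III, Sampling Method and Sample Size Estimation).** The "F-test (ANOVA repeated measures, within-between interactions) is chosen in Gpower software", with "alpha set at 0.05". The text also states "Study power is set at 95" per cent. The "effect size of 0.41 was chosen based on the effect sizes for the primary outcomes of clinical interest from the study" that is cited there. The result is 18 participants, applied as nine patients and nine caregivers per group. Bonferroni is mentioned once, as post hoc analysis to the ANOVA.
- **Outcomes (Table 3, which the Phase III section on clinical effects adopts).** There are six, unranked: TUG, MDS-UPDRS and EQ-5D in patients; knowledge, Zarit burden and EQ-5D in caregivers.
- **Hypothesis.** The null hypothesis covers "improving functions, functional mobility and QoL of persons with PD, carer knowledge, carer QoL and burden among family members of PD" together. The alternate hypothesis is built the same way but leaves out functions. Neither says how many outcomes must show benefit.
- **Analysis (Statistical Tools and Table 6).** "The level of significance is set at *p*<0.05". Table 6 assigns the patient and the caregiver outcomes to the same mixed ANOVA.

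**The concern.** The words primary outcomes occur only in the sample size section, where they describe another study's endpoints. The protocol therefore fixes an error rate, a power and a sample size without saying which outcome of this trial they belong to. It gives no reason why an effect seen in gait-focused physical therapy should apply to caregiver knowledge, burden or quality of life.

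The difficulty comes with a mixed result. If, say, knowledge improves and the other five outcomes do not, the protocol offers no basis for deciding whether the programme was shown to be effective. An ineffective programme has six chances of a nominally significant benefit. If all six were required instead, the quoted 95% would overstate the chance of success. A primary outcome picked after the results are known cannot repair this.

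**Working it through.** **Inputs from the Protocol.** Effect size 0.41, alpha 0.05, power 95%, two groups, N=18 for each outcome (nine per arm), three visits (week 0, week 12, 6-month follow-up), six outcomes.

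**Assumed, because not stated.** Effect size in Cohen's f; correlation between repeated measures rho=0.5; sphericity (epsilon=1). These are the software defaults.

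**1. Reproducing N=18.** For the within-between interaction with k=2 groups and m visits:

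- lambda = f² × N × m / (1 − rho); df1 = (k−1)(m−1); df2 = (N−k)(m−1).
- N=18, m=3: lambda = 0.41² × 18 × 3 / 0.5 = 18.15, with df 2 and 32. Power is 96.2%.
- N=16: power is 93.6%.

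So 18 is the smallest balanced N for one interaction test at the full 0.05. The arithmetic is sound. It depends on rho: the required N is 34, 24, 18 and 12 at rho 0, 0.3, 0.5 and 0.7.

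**2. If any one of six outcomes counts as success.** Under independence, 1 − 0.95⁶ = 1 − 0.735 = 26.5%. Simulating six two-sided tests with a common correlation gives 24.0%, 20.8%, 16.4% and 10.8% at 0.3, 0.5, 0.7 and 0.9.

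**3. If all six must succeed.** Type I error does not inflate. With 95% power each, joint power under independence is 0.95⁶ = 73.5%.

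**4. If alpha is divided over six.** Alpha = 0.05/6 = 0.00833. At N=18, m=3 and rho 0.5, power falls from 96.2% to 84.0%. N=24 (12 pairs per arm) is needed for 95%.

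**5. What N=18 can detect in SD units.** Take arms equal at week 0 and differing by d SD afterwards.

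- Three visits, pattern (0, d, d): f² = ¼ × (4/9 + 1/9 + 1/9)/3 × d² = d²/18, so d = 4.243 f.
- Two visits, pattern (0, d): f² = ¼ × ¼ × d² = d²/16, so d = 4 f.

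Difference needed for 95% power at alpha 0.05:

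| rho | three-visit interaction | week 0 versus week 12 |
|---|---|---|
| 0.5 | f=0.397, d=1.68 SD | f=0.453, d=1.81 SD |
| 0.7 | f=0.307, d=1.30 SD | f=0.351, d=1.40 SD |
| 0.8 | f=0.251, d=1.06 SD | f=0.287, d=1.15 SD |

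For week 0 versus week 12 at f=0.41 and rho 0.5, lambda = 0.41² × 18 × 2 / 0.5 = 12.10 with df 1 and 16. Power is 90.4%, not 95%, and N=22 would be needed for 95%.

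**The case against.** Four objections have force.

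- **Each test is valid on its own terms.** Every single interaction test has a nominal 5% error rate, and about 96% power if f=0.41 holds for that outcome and rho is 0.5. A reader might infer that neither figure attaches to anything the trial could say. That goes too far: the gap is at the level of a confirmatory claim about the programme.
- **The 26% presumes an any-one rule.** The hypothesis joins its outcomes with a conjunction, so an all-must-succeed reading is possible. Error would then be controlled and power would be the problem. This stands, which is why both readings are costed above. The protocol chooses neither.
- **Bonferroni is mentioned.** It is, but without saying which comparisons it covers. A reader might infer that it applies only to comparisons between visits; the text does not say so. What can be said is that no division of alpha across outcomes is stated and that the sample size uses the full 0.05.
- **Multiplicity detail may sit in an SAP that is not shown.** True of the procedure. But the protocol itself fixes alpha, power and N, so the outcome they refer to should be named beside them.

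Two further inferences are tempting and not supported. One is to treat the 4.85 s quoted for TUG as a target and compute power for it. The protocol cites it as a minimal detectable change, which is a measurement-error threshold for an individual, and never as a between-group difference; such a calculation would also need an SD and a correlation that are not given. The other is to read significance into the main trial having nine pairs per arm and the pilot ten. The pilot follows a per-arm rule of thumb and the main trial a power calculation, so the comparison shows nothing about this point.

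**Conclusion.** The point holds. Phase III has six outcomes of equal rank, no primary outcome and no success rule, and its stated alpha, power and sample size rest on a gait-therapy effect size tied to none of them.

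The size depends on how success is read: roughly a 21% to 26% chance of at least one false interaction if any outcome suffices (inter-outcome correlation 0.5 down to 0), or about 74% joint power under independence if all six are required. Higher correlation between outcomes lowers the first figure. The 84% under a six-way split assumes three visits and rho 0.5. The detectable differences of about 1.1 to 1.7 SD (three visits) or 1.15 to 1.8 SD (week 0 versus week 12) cover rho 0.8 down to 0.5, so no single value should be quoted as the trial's sensitivity. A reader might conclude that the sample size was miscalculated. It was not: 18 reproduces for one test, and the fault lies in what it is attached to.

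**What to change.** Before any unblinded results are seen:

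1. Name one primary outcome and one primary contrast. TUG is one candidate, since it is timed by a blinded assessor and lies closest to the gait study behind the 0.41. State whether the contrast is the three-visit interaction or week 0 versus week 12.
2. Make the other five outcomes secondary, either with Holm adjustment or reported as estimates with 95% confidence intervals only.
3. Reword the hypothesis so that the effectiveness claim rests on the primary outcome, and say what the post hoc Bonferroni applies to.
4. Restate the power sentence for the chosen contrast, with the assumed correlation shown. For example, 9 pairs per arm give 95% power for a group difference of about 1.7, 1.3 or 1.1 SD for the three-visit interaction, or about 1.8, 1.4 or 1.15 SD for week 0 versus week 12, at rho 0.5, 0.7 or 0.8. If week 0 versus week 12 is chosen and f=0.41 with rho 0.5 is kept, the stated power should be 90%. The pilot can supply the SD and the correlation.

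The cost is a change of wording. Five outcomes lose stand-alone confirmatory status and the stated power looks less favourable. No extra patients are needed.

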## ASSESSMENT OF PROGRAM SUSTAINABILITY

Program sustainability will be assessed by measuring all participants’ (persons with PD and their family caregiver) outcomes again at a 6-month follow-up and comparing the participants' variables with previously measured data. The aim is to determine if the positive effects of the training program can be maintained at least for 6 months of the program completion. Sustainability also will be measured based on compliance to exercise, adherence to the module component and dropout rate.

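### Intention-to-treat cannot justify a zero dropout allowance, and the mixed ANOVA as described would leave out anyone with a missing visit

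*Protocol*

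**What the plan says.** The Phase III section on sampling method and sample size gives the design inputs: "Study power is set at 95%, alpha set at 0.05 and effect size of 0.41 was chosen" from a cited physiotherapy study, and "F-test (ANOVA repeated measures, within-between interactions) is chosen in Gpower software". It concludes that "a total of 18 participants are required", and plans nine patients and nine caregivers per arm, 36 people in all. On attrition it says: "Dropouts are not considered because intention-to-treat analysis will be used and all participants who are enrolled at baseline" will be in the final analysis.

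Outcomes are measured at week 0, week 12 and a 6-month follow-up (Measurement of outcomes). Figure 6 carries all 36 people to week 12 under intention-to-treat.

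Statistical Tools repeats the intention-to-treat statement, names SPSS and says: "Effects of the interventions and comparison between groups will be analyzed using 6 x 2 Mixed Model ANOVA". Results are to be reported as main effects, the time-by-group interaction and partial eta squared. No imputation is mentioned.

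Dropout is also something the trial sets out to measure. Research question 8 asks about the number of dropouts, Figure 6 and Table 6 list them, and the sustainability section says: "Sustainability also will be measured based on compliance to exercise, adherence to the module component and dropout rate".

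**The concern.** The sample size section treats intention-to-treat as if it removed the effect of attrition. It is a rule about who is analysed and in which arm. If a family does not return at week 12 or 6 months, the rule says the family belongs in the analysis but provides no outcome to analyse.

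The method named does not fill the gap. The G*Power test chosen, together with main effects, interaction and partial eta squared, describes a classical between-within ANOVA. That procedure needs a complete set of visits from each participant in the model. Without imputation, the promise to include everyone enrolled fails once outcomes are missing, and the result would be a completer analysis reported as intention-to-treat.

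Two things are at stake. One is selection bias: the programme is delivered at home by the caregiver and usual care in hospital by professionals (Table 5), so reasons for leaving could differ between arms. The protocol has no data on this, so it is a possibility only. The other is power, because the target is set with no allowance for loss.

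**Working it through.** **Inputs from the protocol.** Alpha 0.05, power 95%, effect size 0.41 (read as Cohen's f, the G*Power input), within-between interaction, two arms, three visits, total 18. Each outcome is analysed in one role only, patient or caregiver, so 18 people, not 36, contribute to each analysis.

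**Inputs assumed.** Correlation between visits r = 0.5 and epsilon = 1. The protocol states neither.

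**Formula.** With k = 2 groups, m = 3 visits and epsilon = 1, the noncentrality is f² × N × m / (1 − r), with df1 = (k − 1)(m − 1) and df2 = (N − k)(m − 1). Power is the probability that a noncentral F exceeds the 5% critical value.

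**Reproducing the planned figure.** For N = 18: 0.41² × 18 × 3 / 0.5 = 18.155, df = 2 and 32, critical F = 3.295, power 96.2%. The smallest N reaching 95% is 17, which equal arms round up to 18. At r = 0.5, two groups with two visits would need 22 and two groups with six measures 12, so the two-group, three-visit layout is the one among these that gives 18.

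**Power by number of complete cases (r = 0.5, epsilon = 1):**

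| Complete cases | Noncentrality | df | Power |
|---|---|---|---|
| 18 | 18.155 | 2, 32 | 96.2% |
| 17 | 17.146 | 2, 30 | 95.0% |
| 16 | 16.138 | 2, 28 | 93.6% |
| 14 | 14.120 | 2, 24 | 89.4% |
| 12 | 12.103 | 2, 20 | 83.0% |

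One incomplete case leaves 95.0%; the second takes power below target.

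**How likely two or more losses are.** The protocol gives no loss rate, so this is a range under independent losses. The chance of at least two incomplete cases among 18 is 23% at a 5% loss rate, 55% at 10% and 90% at 20%.

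**Sensitivity to the correlation.** With 14 complete cases, power is 76.5% at r = 0.3, 89.4% at r = 0.5 and 98.8% at r = 0.7. With all 18 complete it is 87.7%, 96.2% and 99.8%.

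**The case against.** The strongest reply is that no sentence says incomplete cases will be deleted. Missing-data handling is often left to the statistical analysis plan, which is not available here, and values could be imputed before the ANOVA. That stands: deletion is inferred from the named method, and a separate plan could rescue the promise to include everyone. It would not make the stated reason for ignoring dropouts valid, nor recover all the information lost.

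Table 6 lists the pre-post objectives and retention of effect in separate rows. If they are fitted as separate models, someone missing only the 6-month visit stays in the pre-post comparison. That also stands, so the exclusion applies to visits in the model concerned.

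Dropout may mean leaving the programme rather than missing assessments. The sustainability section plans to measure all participants again at 6 months, so continued measurement may be partly intended already. It is not stated for families who stop the module.

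A reader might infer more than the documents support:

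- That 95% power simply fails, or fails with the first loss. It does not: 17 complete cases still give 95.0% under the assumptions that reproduce 18, and with 16 the shortfall is modest.
- That 89% is the power of any analysis with 14 complete cases. It is a complete-case figure. A mixed model that also uses partly observed participants would have a different power.
- That the 90.4% power of a two-visit comparison with all 18 present results from attrition. It comes from having fewer visits.

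**Conclusion.** The point holds in this form. The reason given for a zero dropout allowance is wrong, and the analysis described does not deliver inclusion of everyone enrolled once outcomes are missing, unless imputation is added elsewhere. The protocol also contradicts itself by making dropout an outcome while leaving it out of the sample size.

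The power cost is conditional. With f = 0.41, two groups, three visits, r = 0.5 and epsilon = 1, the design tolerates one incomplete case per outcome. Complete-case power is about 94% with 16, 89% with 14 and 83% with 12. The correlation moves these figures as much as a plausible loss does, and no loss rate is given, so they are a guide and not a forecast. The correction is cheap and should be made before the trial starts.

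**What to change.** Delete the sentence that sets dropouts aside because of intention-to-treat. Then:

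- State that all randomised participants are analysed in their allocated arm with a linear mixed model for repeated measures (REML, small-sample degrees of freedom) using every observed visit. SPSS can fit this.
- State explicitly that outcomes are still measured after a family stops the module.
- Restate the power along these lines: 95% requires at least 17 of 18 complete pairs per outcome, assuming correlation 0.5 and epsilon 1; a complete-case analysis would have about 94% power with 16 and 89% with 14. Label these as complete-case figures, not as the power of the mixed model.

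This needs a change of wording and a little more analysis work, with no new software and no extra participants. The stated power becomes less favourable. If the team would rather keep 18 complete pairs as the target, it should state an expected loss d and enrol 18 / (1 − d): 18 / 0.9 = 20 pairs at 10%, or 18 / 0.8 = 22.5, hence 24 pairs with equal arms, at 20%. Both rates are illustrative.
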